### Blinding

The physical therapist that will conduct the evaluations will be blinded to the group assignment and to the objectives of the study.

To blind the sham group the stimulator will be turned on for only 30 s and then turned off. In this way, the subjects will have the initial sensation associated with electrostimulation but will not receive any stimulation in the remaining time.

### Statistical Analysis

The data will be analyzed by Shapiro-wilk test to determine adherence to the Gaussian curve. If the parametric distribution is confirmed, the data will be expressed as mean and standard deviation, and for non-parametric variables, data will be expressed as the median and interquartile range. The effect size will be calculated based on the difference between means of the preintervention and post-intervention evaluations and will be expressed with their respective 95% confidence intervals.

An ANOVA or the Kruskal-Wallis test will be used for the analysis of the effects obtained in the phases one and two of the study. The Bonferroni correction for multiple comparisons will be employed as a *post-hoc* test. The analyses will be performed considering spatiotemporal gait variables, variables of COP parameters, and EMG signals as the dependent variables. The fixed independent variables in Phase I will be group (congenital and acquired blindness, and sighted), auxiliary resource (with and without guide stick), and shoes (with and without). In Phase II and III, the dependent variables will be the same as described in phase I, and for the fixed independent variables will be groups plus active and sham tDCS groups, evaluation time (preintervention, post-intervention, and follow-up) and group^*^evaluation time interaction. *P* < 0.05 will be considered indicative of statistical significance. The data will be analyzed using the Statistical Package for the Social Sciences (SPSS v.19.0) and Biostat (Analystsoft v. 2008.5.0.1).

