### Evaluation Procedures

All evaluations will be done at baseline and post-immediately therapeutic intervention, Also in 1 and 3 months as follow-ups (Figure 1).

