### Sample Size Estimation

The sample size will be estimated from Phase II where participants will be randomly allocated into four groups (10 each group). Then the calculation will be considering the minimal difference between the mean of an analysis of variance results obtained from both gait speed and the displacement of the center of pressure (COP) as the primary outcome. Thus, the sample size will be estimated with a unidirectional alpha of 0.05 and an 85% statistical power. The sample determined by the calculation will be increased by 20% to compensate for possible dropouts.

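### A Shapiro-Wilk result appears to choose between ANOVA and Kruskal-Wallis in phases 1 and 2, although it does not check what ANOVA needs and a switch would drop the planned group-by-time test

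*Protocol article*

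**What the plan says.** The Statistical Analysis section opens with the normality test: "The data will be analyzed by Shapiro-wilk test to determine adherence to the Gaussian curve". It continues: "If the parametric distribution is confirmed, the data will be expressed as mean and standard deviation", with median and interquartile range for the other variables. The next paragraph says: "An ANOVA or the Kruskal-Wallis test will be used for the analysis of the effects obtained in the phases one and two". No other criterion is given for choosing between the two tests.

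The same section names the model factors. Phase 1 has "group (congenital and acquired blindness, and sighted), auxiliary resource (with and without guide stick), and shoes (with and without". Phases 2 and 3 have treatment group, "evaluation time (preintervention, post-intervention, and follow-up) and group"-by-time interaction. Under Evaluation Procedures the occasions are: "All evaluations will be done at baseline and post-immediately therapeutic intervention, Also in 1 and 3 months as follow-ups", which makes four. Under Sample Size Estimation, phase 2 "participants will be randomly allocated into four groups (10 each group"). The general significance rule is P "< 0.05 will be considered indicative of statistical significance".

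**The concern.** The normality assumption in ANOVA concerns the errors of the fitted model, that is, what is left after group, time and person are accounted for. The null hypothesis of Shapiro-Wilk is that the values form one independent, identically distributed normal sample. Repeated values from the same people are not independent, so a test on values pooled over visits can reject because of clustering even when every component is Gaussian. If each group-by-visit cell is tested instead, each test rests on 10 people, and there are many tests. In neither case does a non-significant result confirm a normal distribution.

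What is at stake is the question each outcome answers. The plan wants a group-by-time interaction. Kruskal-Wallis compares independent groups on one factor; it has no interaction term and no place for repeated measures. If the gate trips for one outcome and not for another, the two are analysed under different hypotheses. Gait speed and centre-of-pressure displacement, together the primary outcome in the Sample Size Estimation section, could part company in this way.

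**Working it through.** The plan gives no figure on this point, so there is none to reproduce. The check asks how often Shapiro-Wilk rejects data that are exactly Gaussian, under each way the sentence could be carried out.

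**Inputs from the article.** 4 groups x 10 people = 40 participants; 4 occasions; 40 x 4 = 160 values per variable; 4 x 4 = 16 group-by-visit cells; significance at 0.05, assumed to apply to Shapiro-Wilk as well.

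**Assumptions not in the article.** Within-person correlation r from 0.5 to 0.9 (0.95 as an extreme), equal between all visits; total SD 1 within each cell. Each value is group mean + time mean + person effect (variance r) + error (variance 1 - r), all normal. Rates come from 1,500 to 4,000 simulated data sets per scenario; separate runs agree to within a few percentage points.

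**Reading A: one test on all 160 values, no mean differences.**

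| r | Gaussian data rejected |
|---|---|
| 0 | 5% |
| 0.5 | 7-8% |
| 0.7 | 17% |
| 0.8 | 25-27% |
| 0.9 | 42-43% |

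**Reading B: one test per cell, any rejection counts.** If the tests were independent: 1 - 0.95^16 = 56%. Simulated with correlated visits: about 50% (48% to 57% across the range). Within one cell, raw values and residuals differ only by a constant, so this excess comes from repeated testing and not from using raw values.

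**Reading C: one visit, four groups pooled.** With two groups shifted, rejection is 4-5% for shifts up to 2 SD. It rises to 26% at 3 SD and 79% at 4 SD. One test at each of four visits, any rejection counting: 11% to 20% (independence: 1 - 0.95^4 = 19%).

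**What cures it.** On residuals with both cell means and person effects removed, Gaussian data are rejected 3% to 5% of the time in every scenario run. Removing cell means alone does not help: 26% at r = 0.8 and 59% at r = 0.95.

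**What a switch costs.** Phase 2 layout, Gaussian data, one group shifted by an assumed 0.8 SD at all visits after baseline. The intended comparison was represented by a test of change from baseline across groups; the gated version uses Kruskal-Wallis on the post-baseline mean whenever the pooled Shapiro-Wilk rejects. For r from 0.7 to 0.9, power is about 80% to 99.9% for the change-based test and about 73% to 81% when gated. The loss grows with r, because the gate trips more often and the between-group rank test makes no use of the baseline. At r = 0.5 the gate trips in only about 8% of data sets and no loss was visible.

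**The case against.** The strongest reply is that the only written consequence of the test is the choice of summary statistic. No sentence says that it selects the analysis, and the article does not say whether raw values or residuals are tested, pooled or by group. A condensed article may leave that to a fuller document. This stands as a limit on certainty. Even so, the text speaks of a distribution being confirmed and then offers two tests with no other rule for choosing, so a normality gate is how most readers would carry it out.

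Several stronger readings are tempting, and the documents do not support them.

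- A reader might infer that Gaussian data are often sent to the rank test. That holds for pooling over visits with high correlation, or for an any-cell rule. It does not hold at a single visit with moderate differences.
- A reader might infer that skew is mostly missed. One cell of 10 lognormal values (log-SD 0.5, assumed) is flagged only about 24% of the time. Under the any-of-16 rule that gives the 50% false-alarm rate, the same skew would be flagged in about 1 - 0.76^16 = 99% of trials if cells were independent. The two rates belong to different decision rules and cannot be set side by side.
- A reader might infer that the 0.05 level and the 85% power in Sample Size Estimation are void. At one visit with 4 groups of 10, the gate hardly matters. The Gaussian null error is 4.6% with or without a by-group gate, and 5.2% against 5.1% with a pooled gate. With lognormal data (log-SD 0.5) the gated error is 5.7% or 4.1%. Power for a 1.3 SD shift in one group is 81% gated against 82%. Also, the two named tests are written for phases 1 and 2, while the power figure sizes phase 3.
- A reader might infer that the reported effect measure changes with the gate. The section bases the effect size on pre-to-post mean differences, without any condition on normality.

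None of this answers the main point: in the repeated-measures layout that the plan specifies, Kruskal-Wallis does not test the planned interaction.

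**Conclusion.** The concern holds in a limited form. A normality test on unspecified data appears to pick the analysis in phases 1 and 2, it does not address the errors that ANOVA depends on, and a pass at 10 per group confirms nothing. False rejection of Gaussian data is about 7% to 43% if values are pooled over visits (correlation 0.5 to 0.9), about 50% if any cell counts, and near nominal at a single visit. The consequence that matters is the change of hypothesis when the switch occurs, with a power loss in phase 2 that is absent at low correlation and considerable at high correlation. The conclusion rests on the gate being the intended rule, and its size rests on the assumed correlation, effect and mode of application, none of which the article gives. For phase 3 the article lists the factors but names no test, so the finding is not extended to it as a stated rule.

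**What to change.** Remove Shapiro-Wilk as the rule that chooses the test. For each outcome, fix one repeated-measures model in advance, with group, time and group-by-time interaction and a participant effect. In phase 1, do the same with the factors listed there. Check the residuals of that model, with the subject effect removed, by plots; residuals from cell means alone are not enough. Keep a rank-based or bootstrap version that answers the same group-by-time question as a sensitivity analysis. Shapiro-Wilk may stay as a description of those residuals, provided that it triggers no switch.

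A log scale for positive measures expected to be skewed, such as centre-of-pressure area or EMG amplitude, is optional, since the article gives no distributions. If it is wanted, it should be fixed per outcome before unblinding.

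The cost is a change of wording in the Statistical Analysis section; no extra data or visits are needed. The small downside is that any log-scale results are reported as ratios.

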Studies reported positive clinical effects with the use of tDCS combined with rehabilitation programs. In a meta-analysis (7) tDCS improved PC through the modulation of cortical excitability, which this technique could be a choice to enhance functionality and independence, and thus, reduce the rate of falls in individuals with a balance disorder, mainly on primary motor cortex (M1) stimulation. However, the effects of tDCS on the cerebellar cortex should be better investigated due to divergence in the study results. Are recognized that both early and late blind people have morphological changes in their whole brain, and the cerebellum is one of these structures. For example, Kosif et al. (8) showed a smaller volume of cerebellar area in congenital blindness subjects compared to sighted subjects. But systematic review studies showed positive effects of cerebellar tDCS to modulate cerebellocerebral networks (9, 10). But until the present, no study has investigated the effects of cerebellar tDCS on gait and PC in blind people.

As stated earlier for the visually impaired people, motor control is quite challenged even in simple tasks that require PC due to their blindness, and that tDCS induces cerebellar excitability changes (11), in which can modulate cerebellar-motor cortex excitability and thus, affect positively PC processing (12). The present study hypothesizes that tDCS can potentiate the effects of a proprioceptive exercises on both static and dynamic PC in blind subjects. The secondary objectives are (1) to determine possible differences in PC betweenindividuals with congenital and acquired blindness; (2) to evaluate the motor pattern of gait with and without the use of a guide stick when wearing shoes or while barefoot; and (3) to analyze whether proprioceptive exercises with or without tDCS can lead to different results with regard to PC.

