### Ethical Approval and Consent to Participate

All procedures were performed following the Guidelines and Regulating Norms of Research involving human beings, formulated by the Brazilian National Health Council—Health Ministry of Brazil, established in 2012. This study received approval from the Human Research Ethics Committee of the Nove de Julho Educational Association (No. 1.672.635/2016). The study protocol was registered in the Clinical Trial Registration (number NCT03173105). All participants and/or their person in charge must agree to take part in the study by signing an Informed Consent Form. In addition, any personal data as well as the participants' identities, based on the ethical principles of confidentiality and privacy, will be guaranteed absolute secrecy. Sham intervention procedures will always be performed in association with an active treatment, which makes its use of less impact to the patient.

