### Randomization

A randomization in blocks will be applied, in which the participants will be randomly allocated to one of the four groups: (G1 = active tDCS + dynamic proprioceptive exercises; G2 = sham tDCS + dynamic proprioceptive exercises; G3 = active tDCS + static proprioceptive exercises; and G4 = sham tDCS + static proprioceptive exercises). Randomization will be done at the website www.random.org and conducting by a person blind to the objectives and protocol of this study.

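### The plan's only defined effect size and 95% CI is a pre-to-post difference, which mixes exercise change with any tDCS effect and does not estimate the hypothesised effect of tDCS

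*Protocol article*

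**What the plan says.** The Statistical Analysis section defines one effect measure: "The effect size will be calculated based on the difference between means of the preintervention and post-intervention evaluations". These effect sizes "will be expressed with their respective 95% confidence intervals". The sentence names two evaluations and no groups. No active-minus-sham estimate with an interval is defined elsewhere in the article.

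The next paragraph of that section sets out the Phase II and III analysis: "for the fixed independent variables will be groups plus active and sham tDCS groups, evaluation time", followed by the "group^*^evaluation time interaction".

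The Introduction gives the hypothesis: "The present study hypothesizes that tDCS can potentiate the effects of a proprioceptive exercises on both static and dynamic PC in blind subjects". Under Randomization, each exercise type has an active and a sham tDCS arm; the dynamic control, for example, is "G2 = sham tDCS + dynamic proprioceptive exercises". The ethics section confirms the pairing: "Sham intervention procedures will always be performed in association with an active treatment". The Discussion cites a study in which balance training over 6 weeks improved balance in blind adults.

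**The concern.** The hypothesis is about a difference between arms: how much tDCS adds to exercise. The effect size as worded is a difference between time points. Since every participant exercises, and the article's own Discussion leads the reader to expect exercise to help, a pre-post gain is likely in all four arms even if tDCS does nothing.

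What is at stake is the number that readers will carry away. An interaction test gives a p-value. If group has four levels and all four visits are used (baseline, post-intervention, 1 and 3 months), that test has (4 − 1) × (4 − 1) = 9 degrees of freedom, and it gives neither direction nor size for active versus sham. The estimate with an interval would be the pre-post one. A report could then show an active-arm interval clear of zero beside a null interaction, and the first could be taken as evidence for tDCS.

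**Working it through.** **What the plan gives.** There is no figure to reproduce: the article states no effect size, SD, pre-post correlation or Phase III sample size. The one usable input is the Phase II size of 10 per group (Sample Size Estimation).

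**What each quantity estimates.** Let *e* be the change due to exercise and practice, and *t* the effect of tDCS, both at post-intervention.

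- Pre-post change, active arm: *e* + *t*
- Pre-post change, sham arm with the same exercise: *e*
- Active minus sham: (*e* + *t*) − *e* = *t*

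Only the last is the hypothesised quantity. The pre-post figure exceeds it by *e*, whatever the value of *t*.

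**Illustration. These inputs are assumptions, not in the documents:** SD of 1 at each visit; pre-post correlation ρ of 0.5 to 0.7; *e* of 0.2 to 0.8 SD; *t* = 0.

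- SD of change = √(2(1 − ρ)): 1.000 at ρ = 0.5; √0.6 = 0.775 at ρ = 0.7.
- SE of mean change, one arm of 10 = SD of change/√10: 0.316 and 0.245.
- 95% CI half-width, t quantile on 9 df = 2.262: 2.262 × 0.316 = 0.72 and 2.262 × 0.245 = 0.55.
- At *e* = 0.5 and ρ = 0.7, the expected interval is 0.5 ± 0.55, or −0.05 to 1.05.

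The probability that the pre-post 95% CI excludes zero although *t* = 0 comes from the noncentral t distribution with noncentrality *e*/SE:

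| *e* (SD) | ρ = 0.5 | ρ = 0.7 |
|---|---|---|
| 0.2 | 0.09 | 0.11 |
| 0.5 | 0.29 | 0.45 |
| 0.8 | 0.62 | 0.83 |

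Under the same assumptions the active-minus-sham difference in change has expectation 0, and its 95% CI excludes zero in 5% of trials, by construction.

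Pooling the two active arms (n = 20) would strengthen the contrast. At *e* = 0.5 and ρ = 0.7 the SE is √(0.6/20) = 0.173, the interval is 0.5 ± 2.093 × 0.173, or 0.14 to 0.86, and zero is excluded in about 78% of trials. The plan does not say that it will pool the dynamic and static arms, so the single arm of 10 is the fairer case.

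**If tDCS does work.** With *t* = 0.3 SD, also assumed, the active-arm pre-post figure would be 0.2 + 0.3 = 0.5 to 0.8 + 0.3 = 1.1 SD, against a tDCS effect of 0.3 SD.

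**Choice of between-arm estimator.** The error variance of a change-score comparison is proportional to 2(1 − ρ), and that of a baseline-adjusted comparison to 1 − ρ². At ρ = 0.7 these are 0.60 and 0.51, a ratio of 0.85. Both estimate *t*, and adjustment is somewhat more precise.

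**The case against.** The strongest reply is that the same section already contains the right comparison. Active and sham groups, time and their interaction are in the Phase II and III analysis, and that interaction asks whether change differs between randomised arms. If tDCS does nothing, the test rejects at its nominal rate however well exercise works. This stands. A reader might infer that the plan discards the randomisation, or that it is bound to credit tDCS with the exercise effect. Neither follows, because the test uses the sham arms and nothing in the text says that the pre-post figure will be attributed to tDCS.

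Second, the article does not say that the effect size is calculated within groups and does not name it as the main estimate. The sentence sits among the descriptive summaries, and an effect size built on change scores and then compared between arms is a possible meaning. This stands in part. The sentence mentions no comparison of arms, and pooling across arms would leave active and sham indistinguishable. Within-arm change remains the natural reading, and a reader cannot be left to guess otherwise.

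Third, one might add regression to the mean to what the pre-post figure contains. The documents give little support for this: entry is by eye diagnosis, with no balance or gait threshold.

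Fourth, one might infer that Phase III will be sized on the pre-post figure. The Sample Size Estimation section refers to a difference between means from an analysis of variance and does not say so.

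Finally, the article is condensed and the detail may be elsewhere. That excuses silence, but here the article does define the effect size, on a contrast that does not match its hypothesis.

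**Conclusion.** The point holds for the effect estimate and its confidence interval. As worded, they measure exercise and practice change plus any tDCS effect, and so do not estimate what the trial sets out to show. It does not extend to the significance test.

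The direction is certain: any benefit from exercise or practice enlarges the active-arm figure beyond the tDCS effect. The size cannot be derived from the documents. Under the assumptions in the working, an active arm of 10 with no tDCS effect would show an interval clear of zero in about 9% to 83% of trials. That is the power to detect a genuine pre-post change. It becomes an error about tDCS only if the interval is read without the sham arm and the interaction.

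**What to change.** Replace the effect-size sentence with wording to this effect:

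> The effect size is the difference between active and sham tDCS in mean change from baseline (or the baseline-adjusted mean difference) at post-intervention and at 1 and 3 months, with its 95% confidence interval. Pre-to-post changes within each arm are reported descriptively.

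This puts the estimate in line with the group-by-time analysis already planned. The difference in change is enough to repair the error. The baseline-adjusted version is usually more precise and is a preference, not a requirement. The cost is one sentence, and all the data are already to be collected at the scheduled visits.

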#### Timed Up and Go (TUG) Test

The participants will be instructed to perform the test at a safe, self-selected pace. Blind subjects will be guided under the voice command of the researcher signaling the moment to turn around, and then to return to a seated position in the chair. Velcro strips were attached to the wall ~12–18 inches from the chair to serve as a “prompt” that the chair was nearby. The participants will be instructed to perform this task at a safe pace but were told that their time was recorded (13). The TUG test will be performed with shoes and barefoot with and without a guide stick.

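### Kruskal-Wallis, named as the alternative to ANOVA for Phases I and II, cannot fit the repeated, multi-factor analyses listed beside it, and no participant term is named for the ANOVA

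*Protocol article*

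**What the plan says.** All references are to the protocol article.

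- **Test (Statistical Analysis).** "An ANOVA or the Kruskal-Wallis test will be used for the analysis of the effects obtained in the phases one and two". The sentence does not mention Phase III, and no later sentence names a test for it.
- **Normality check (same section).** "The data will be analyzed by Shapiro-wilk test to determine adherence to the Gaussian curve". The text then ties the result to how data are summarised. That it also decides between the two tests is implied, not stated.
- **Phase I factors (same section).** Besides group (congenital blindness, acquired blindness, sighted), it lists "auxiliary resource (with and without guide stick), and shoes (with and without").
- **Phase II and III factors (same section).** Group, active or sham stimulation, and "evaluation time (preintervention, post-intervention, and follow-up) and group^*^evaluation time interaction". All factors are called fixed independent variables.
- **Visits (Evaluation Procedures).** "All evaluations will be done at baseline and post-immediately therapeutic intervention, Also in 1 and 3 months as follow-ups".
- **Conditions (Timed Up and Go).** "The TUG test will be performed with shoes and barefoot with and without a guide stick". For gait and postural control, Sample and Recruitment describes the same stick and shoe comparison, which makes repetition on the same person likely there too.
- **Phase II size (Sample Size Estimation).** "participants will be randomly allocated into four groups (10 each group"). The Phase III size is to be calculated from Phase II analysis-of-variance results on gait speed and centre-of-pressure displacement.

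The article nowhere mentions a repeated-measures or mixed model, a within-person factor, a participant effect, or a rank test for related samples.

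**The concern.** The question the trial asks is whether stimulation adds to the effect of exercise. With a baseline and later evaluations on the same people, that is a group-by-time question. Kruskal-Wallis has one grouping factor, treats all observations as independent, and has no interaction term. If it is used for an outcome in Phase I or II, the analysis that the section lists for that outcome cannot be carried out.

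For the ANOVA, what matters is which error term is used. Differences between people belong in the error for group comparisons and should be removed from the error for time, stick, shoe and interaction comparisons. One pooled error gets both wrong, in opposite directions: group differences look too certain, and the interaction becomes almost undetectable. Phase II results also set the size of Phase III, so a wrong variance there could affect more than the pilot.

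**Working it through.** The article states no error rate, power or computed sample size on this point, so there is no figure to reproduce. The check uses the article's own layout.

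**Inputs from the article.** 4 groups of 10 people (Sample Size Estimation); 4 evaluations (Evaluation Procedures); significance level 0.05 (Statistical Analysis).

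**Assumed inputs.** Within-person correlation ρ, varied from 0 to 0.9 and equal for all pairs of visits; normal data with variance 1; no dropout; the effect sizes below.

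**Step 1: degrees of freedom.** There are 4 × 10 × 4 = 160 records. An ordinary factorial ANOVA has a single error with 160 − 16 = 144 df. A repeated-measures (split-plot) ANOVA divides this into 40 − 4 = 36 df between people and 36 × 3 = 108 df within people.

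**Step 2: expected mean squares with no true effects.** Between people: 1 + 3ρ. Within people: 1 − ρ. Pooled: [36(1 + 3ρ) + 108(1 − ρ)] / 144 = 1. So with a pooled error the group F ratio is inflated by about 1 + 3ρ (1.9, 2.5 and 3.4 at ρ = 0.3, 0.5 and 0.8). The time and interaction ratios shrink by 1 − ρ (0.7, 0.5 and 0.2).

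**Step 3: simulated type I error at nominal 0.05 (10,000 runs per setting).**

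| Test | ρ = 0 | ρ = 0.3 | ρ = 0.5 | ρ = 0.8 |
|---|---|---|---|---|
| Group, pooled error | 0.05 | 0.25 | 0.36 | 0.51 |
| Time, pooled error | 0.05 | 0.013 | 0.002 | <0.001 |
| Group × time, pooled error | 0.05 | 0.0045 | 0.0006 | <0.001 |

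With split-plot errors, all three tests stay between 0.047 and 0.054 for every ρ from 0 to 0.9. With three evaluations instead of four, the pooled group test still gives 0.18, 0.27 and 0.37 at ρ = 0.3, 0.5 and 0.8.

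**Step 4: illustrative group × time power.** One group is shifted by 0.8 SD at every post-baseline visit.

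| Error term | ρ = 0.3 | ρ = 0.5 | ρ = 0.8 |
|---|---|---|---|
| Pooled | 0.07 | 0.02 | 0.0004 |
| Split-plot | 0.26 | 0.38 | 0.83 |

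**Step 5: Kruskal-Wallis on the stacked records (2,000 runs).** With no effect, the test by group rejects at 0.23, 0.38 and 0.51, and the test by time at 0.009, 0.001 and 0.000 (ρ = 0.3, 0.5, 0.8). With a pure crossover interaction of 1 SD, the test by time rejects in at most 0.05% of runs. The test by group rejects in 27% to 40% (ρ = 0.5 and 0.8), no more than the 38% to 51% seen with no effect at all. Neither detects the interaction. Applied to each person's change from first to last evaluation, Kruskal-Wallis rejected in every run, but the article plans no such test.

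**The case against.** The strongest reply is that the article never says the ANOVA is an ordinary one. It gives no type; time and stick are properly called fixed factors in a repeated-measures or mixed model too; and a condensed article may leave the error structure to the full protocol or analysis plan. This stands. A reader might infer from the pairing with Kruskal-Wallis, the rank counterpart of an independent-groups ANOVA, that independence is assumed throughout. That is a natural reading but not a stated one, so the ANOVA figures are conditional.

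Other stronger readings also go too far:

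- **That the trial is left with no test of its hypothesis.** The test-naming sentence covers Phases I and II. Kruskal-Wallis is not assigned to Phase III, the main trial; the gap there is that no test is named.
- **That a failed normality test automatically triggers Kruskal-Wallis.** The article links normality explicitly only to the choice of summary statistics.
- **That Kruskal-Wallis can never address group by time.** On change scores it can test one such contrast, though none is planned.
- **That three time levels contradict four visits.** Evaluation Procedures calls both later visits follow-ups, so the third label may cover both.

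In Phase I, repetition across stick and shoe conditions is explicit only for the Timed Up and Go test, which is not among the dependent variables that Statistical Analysis lists. For gait and postural control it is likely but inferred.

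None of this rescues Kruskal-Wallis. Whatever ANOVA is meant, the named alternative does not fit the listed factors, and this is a choice the article makes, not a detail it omits.

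**Conclusion.** Wrong as written, in two parts of different strength.

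1. **Unconditional.** Kruskal-Wallis, as named for Phases I and II, cannot deliver the three-factor Phase I analysis or the Phase II group-by-time interaction, and does not allow for repeated visits. This needs no assumption about the data.
2. **Conditional on a pooled error term.** If the ANOVA is run as an ordinary factorial one, with ρ between 0.3 and 0.8, group comparisons carry about 25% to 51% false positives. The interaction test rejects in under 0.5% of null trials, and in the example its power falls from 0.26–0.83 to 0.07 or less. The correlation and effect size are assumptions, and at ρ = 0 the problem vanishes. If a repeated-measures ANOVA was intended, the article only needs to say so.

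The effect on the Phase III sample size is a possibility, since the article does not spell out which Phase II quantities enter that calculation.

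**What to change.** In Statistical Analysis, state that Phases I, II and III are analysed with a linear mixed model, or a repeated-measures ANOVA, with a participant term. For Phase I, make stick and shoes within-person factors and group a between-person factor. For Phases II and III, make evaluation time a within-person factor, keep the group-by-time interaction, and list the evaluations that enter. Extending the sentence to Phase III also closes the gap there.

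Replace Kruskal-Wallis with an alternative that respects the repeated structure, such as a transformation of the outcome or a participant-level permutation or bootstrap test. Which of these is used is the sponsor's choice.

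The cost is analysis wording only: no change to recruitment, visits or measurements, and the stated software can fit such models. A mixed model also keeps participants who miss a follow-up visit. The change should be made before Phase II is analysed, because Phase III is sized from it.
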